### **10.3 Data transfer (handling, processing and storage)**

In the study, basic demographics, name, and alcohol history together with drinking history will be collected from patients in accordance with the patient consent form, patient information sheet and sections 6.3, 6.4 and 6.5 of this protocol.

The basic demographics, name, and alcohol history together with drinking history will be appropriately sent to PHARMExcel Ltd for study monitoring and to [name] [name] for statistical analysis. [name] and [name] will act as the data controllers of such data for the study.

[figure not shown]

[name] and [name] will process, store and dispose of basic demographics, name, and alcohol history together with drinking history, in accordance with all applicable legal and regulatory requirements, including the Data Protection Act 1998 and any amendments thereto.

#### **10.4 Access to Data**

Direct access will be granted to authorised representatives from the Sponsor, host institution and the regulatory authorities to permit trial-related monitoring, audits and inspections.

#### **10.5 Archiving**

UCL and each participating site recognise that there is an obligation to archive study-related documents at the end of the study (as such end is defined within this protocol). The Chief Investigator confirms that he/she will archive the study master file at Royal Free Campus, UCL for the period stipulated in the protocol and in line with all relevant legal and statutory requirements. The Principal Investigator at each participating site agrees to archive his/her respective site's study documents for 5 years and in line with all relevant legal and statutory requirements.

### **11 MONITORING, AUDIT & INSPECTION**

Since this is a low-risk trial, monitoring will be limited to a single data monitoring visit, by a contract research organisation (Pharmexcel Ltd) prior to the completion of the study.

### **12. INSURANCE**

University College London (UCL) holds insurance against claims from participants for injury caused by their participation in the trial. Participants may be able to claim compensation if they can prove that UCL has been negligent. However, as this trial is being carried out in a hospital, the hospital continues to have a duty of care to the participant of the trial. University College London does not accept liability for any breach in the hospital's duty of care, or any negligence on the part of hospital employees. This applies whether the hospital is an NHS Trust or otherwise.

Participants may also be able to claim compensation for injury caused by participation in this trial without the need to prove negligence on the part of University College London or another party. Participants who sustain injury and wish to make a claim for compensation should do so in writing in the first instance to the Chief Investigator, who will pass the claim to the Sponsor's Insurers, via the Sponsor's office.

Hospitals selected to participate in this trial shall provide negligence insurance cover for harm caused by their employees and a copy of the relevant insurance policy or summary shall be provided to University College London, upon request.

[figure not shown]

The manufacturer, CyberLiver, holds indemnity to cover the malfunction and breakdown of the device.

[figure not shown]

## 13. APPENDICIES

### 13.1 Appendix 6 – Amendment History

| Amendment No. | Protocol version no. | Date issued | Author(s) of changes | Details of changes made |
|---------------|----------------------|-------------|----------------------|-------------------------|
|               |                      |             |                      |                         |

[figure not shown]

Topic Guide: AlcoChange Study (IRAS: 190682).

Authors: [name], [name]

Thank you so much for your time and for coming along to talk with us today. My name is [name] and I am a research intern here at the royal free.– The aim today is to get a deeper understanding of your experience with AlcoChange and finding out what we can change to make the app more useful for you (and other people like yourself in the future)

- Go through information sheet
- Go through consent form – have them sign it

The plan for this afternoon is to firstly discuss your experience with alcohol and ARLD and the steps you have taken in the past to stop drinking.

Following this we will discuss your experience with the app and what potential improvements could be made to it in the future.

Does that all sound ok?

Before we start it is important for you to know that there are no right or wrong answers. We are just exploring this topic and are really interested in hearing about your opinions. If you don't feel comfortable answering any questions, you don't have to.

This is just a relaxed discussion so respect opinions and let everyone have their say. Listen / talk to each other not me. Everything discussed here today will be confidential.

Do you have any questions before we start? This session will be recorded is that ok - all names will be anonymized.

Turn on recorder.

Have people introduce themselves (use name tags)

1. Why did you decide to take part in this study?
2. Can you tell me a bit about your usual drinking patterns?
  - ↳ Potential probes:
    - ↳ How long have you experienced this...?
    - ↳ How serious would you say this is for you?
    - ↳ Does this have an impact on your day to day life?
    - ↳ When were you first diagnosed with ARLD
3. What were your motivations for taking part in the study?

4. What prompted/motivated you to want to achieve abstinence?  
(Ask about context of experiences)
5. What steps have you taken in the past to stop drinking?
  - ↳ Prompt: which did you find most useful – what was your longest period of abstinence achieved?
  - ↳ What triggers you to resume drinking?
- Were you engaging with any other services or using any other tools whilst on the AlcoChange?

**Prompt: If you have used other alcohol services or face to face support groups – how do you think AlcoChange compares in terms of how effective it was?**

#### **QUESTIONS RELATED DIRECTLY TO THE APP**

6. Overall, what do you think of the app – has it been helpful / unhelpful?
7. How often did you use it?
  - ↳ Probe: did certain events or times make you use it more
8. How long did it take for you to learn how to use this application?
  - ↳ Prompt. If necessary, – What kind of work and skills are needed to use the application well?
9. What benefits, if any, did you get from using the app?
10. Do you think this app has any drawbacks – or aspects you found difficult?
11. Have you ever used an app to manage your drinking before?
  - ↳ Prompt: if so how do they compare
12. Would you recommend the app to a friend?

#### **FEATURES**

13. Which features did you dislike
  - ↳ Prompt: did you use these the least?

Topic Guide: AlcoChange Study (IRAS: 190682).

Authors: [name], [name]

14. Which features did you particularly like?
15. How user-friendly would you say it is?
16. Was there anything that made you unsure about using the app?

#### **SPECIFIC FEATURES [Now let's chat about some of the specific features of the app...]**

17. What were your thoughts on the breathalyzer feature?
  - ↳ Did you use it regularly
  - ↳ Did you find it helpful/not helpful etc...
18. Did you ever contact the helpline or a friend through the app –
  - ↳ Prompt: If so, how was that?
19. Did you log your appointments on the app calendar
20. Did you regularly log cravings? / ➔ if so did this help you overcome them
21. Did you log when you had a drink?

#### **POTENTIAL IMPROVEMENTS [Now let's chat about potential improvements to...]**

22. What are your thoughts on how we could improve AlcoChange
23. Are there any features you would like to see added?
  - ↳ Probe: Can you tell me more about that

#### **BEHAVIOUR CHANGE:**

1. What changes in your behaviour did you have to make while using the application?
  - ↳ Prompt: If necessary, how has use of this application influenced your drinking habits.
  - ↳ Prompt: Did any specific features help bring this changes about....
2. How easy was it to adopt these changes?
  - ↳ Prompt: What other support did you draw on, in addition to this app?
3. Do you feel you have learned anything from using Alcochange?
  - ↳ Probe: Can you tell me more about that?

Topic Guide: AlcoChange Study (IRAS: 190682).

Authors: [name], [name]

*MAY ALSO WANT TO ASK, what impact (if any) has it had on their life –*

4. Has using Alcochange had any impact on your...
  - i. work life
  - ii. social life and relationships (family, partners, friends)
  - iii. (perceived) psychological impact (mental health and well-being)
  - iv. physical health etc
  - ↳ Probe: Can you tell me more about that?
  - ↳ Probe: What exactly was that impact?
  - ↳ Prompt: How do you think has Alcochange helped achieve this impact
  - ↳ Prompt: Do you think this impact was short-lived or will it be sustained

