| Secondary                          | 
 
- Compliance with the device.
 
- Attendance at community alcohol services following discharge.
 
- Change in health related quality of life (HRQoL)
 
- Changes in patient empowerment
 
- Factors determining compliance with app and effect on drinking behaviour
 
 | 
 
- No of interactions with the device over the study period.
 
- Follow-up rates at community alcohol services appointments over the study period.
 
- HRQoL will be assessed by SF-36 questionnaire before and after the study period.
 
- Patient empowerment will be assessed by the SUSTAINS questionnaire.
 
- Qualitative assessment at focus group
 
 |
| Tertiary / exploratory             | 
 
- Presence or absence of periodontitis in patients with ALD
 
- Change in microbial population in saliva and stool over study period
 
- Frequency of hospital admissions up to 1 year due to
 
                                                                                      | 
 
- Dental examination at baseline
 
- Sampling of saliva and stool at baseline and at 3 months
 
- Hospital Episode Statistics (HES) data to determine subsequent hospital admissions up to 1 year.
 
                                                                                                                                                                     |

[figure not shown]

|  |                        |  |
|--|------------------------|--|
|  | a complication of ALD. |  |
|--|------------------------|--|

[figure not shown]

|                     |                                                                                                                                                                                                                                                |
|---------------------|------------------------------------------------------------------------------------------------------------------------------------------------------------------------------------------------------------------------------------------------|

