#### 3.2 Secondary objectives / outcome measures

The secondary objectives will assess compliance with the AlcoChange device, attendance at community alcohol services, and assessment of health related quality of life (HRQoL) and patient empowerment.

Compliance with the AlcoChange device will be assessed by quantifying the number of interactions with the device by the patient over the 3-month study period.

Attendance at community alcohol services following discharge from hospital will be assessed by direct contact with the community alcohol centre at the end of the study period (list of community

---

 Note the research team will contact the community alcohol services directly at the end of the study to gather information on community attendances. The community services will not have any involvement in the study or any access to study information.

[figure not shown]

alcohol centres attached). Current non-attendance rates following discharge from hospital are ~50%.

Health-related quality of life (HRQoL) and patient empowerment will be assessed by questionnaires, which will be administered at baseline and at the end of study follow-up appointment at 3 months. The SF-36 questionnaire will be used to assess HRQoL, and patient empowerment will be assessed by the SUSTAINS questionnaire which is designed and validated to assess the impact of e-health interventions on patient empowerment and relationship with health services.

Qualitative research methodologies will also be used in order to gain deeper understanding of facilitating factors and barriers to use of the app, and factors which influence drinking behaviour. Study participants will be contacted by telephone, and asked for their willingness to participate in a focus group to explore the above issues. Two focus groups will be conducted, with four to six participants in each group. Each will last up to one hour and a half. A topic guide will be developed to direct the focus groups. Participants will be asked for their thoughts about facilitators and barriers to use of the AlcoChange app, and factors that influenced changes in drinking behaviour. Specific interactions between use of the app and factors that influenced changes in drinking behaviour. Specific interactions between use of the app and changes in drinking behaviour will be explored.

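### The focus-group guide's behaviour-change questions assume that change occurred, leave the app's effect on drinking to an optional prompt, and never ask why use fell or stopped

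*Combined protocol and SAP*

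**What the plan says.** The Trial Summary lists as a secondary objective "Factors determining compliance with app and effect on drinking behaviour" and gives focus-group assessment as its outcome measure. The objectives table in protocol section 3 repeats that pairing. Section 3.2 says participants will be asked about "facilitators and barriers to use of the AlcoChange app, and factors that influenced changes in drinking behaviour", and adds that the link between app use and changes in drinking will be explored specifically. On format, "Two focus groups will be conducted, with four to six participants in each group" and "Each will last up to one hour and a half".

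The focus group topic guide puts this into practice as follows.

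- Behaviour change, item 1: "What changes in your behaviour did you have to make while using the application". A prompt beneath it, marked for use only if needed, asks "how has use of this application influenced your drinking habits".
- Behaviour change, item 2: "How easy was it to adopt these changes".
- Questions related directly to the app, question 7, asks how often the app was used. Its one probe is "did certain events or times make you use it more".

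**The concern.** A question that takes change for granted invites participants to supply one. Someone whose drinking did not change, or increased, has to contradict the premise in front of other participants and a moderator who, by the guide's script, is a research intern at the treating hospital. The study is single-arm, so no comparison group would show how much of the reported change arises without the app.

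The objective also has two halves, compliance and effect on drinking. If the direct question on drinking is optional, one group may be asked it and the other not. If only increased use is probed, reasons for disengaging emerge only when a participant volunteers them. Section 4 says that findings on drinking, compliance and acceptability will determine whether a randomised trial is feasible, so one-sided answers here would carry forward.

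**Working it through.** The plan gives no figure for this point, so the check compares the objective with the guide and then tests the time available.

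**1. Effect on drinking.** Section 3.2 promises to explore how app use and drinking changes interact. Of the guide's 29 numbered questions, none asks whether drinking changed during the study. Questions 2 and 5 concern usual patterns and past attempts to stop. A prompt under question 5 compares AlcoChange's effectiveness with other services, and question 20 asks whether logging cravings helped. The only item that asks directly about the app's influence on drinking habits is the conditional prompt under item 1.

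**2. Wording of the block.** Items 1 and 2 contain no qualifier such as 'if any'. The guide does use that qualifier at question 9 and in the note before item 4, so the neutral form was available and was not used here. A further prompt under item 1 asks whether particular features helped bring the changes about, which again starts from change.

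**3. Reduced use.** Question 7 probes in one direction. Question 10 asks about drawbacks and difficulties, question 13 about disliked and least-used features, and question 16 about hesitancy. These cover barriers, but none asks why overall use declined or ended.

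**4. Whether the unasked answers are realistic.** Table S2 puts 18 of 41 completers below 30 logins: 18/41 = 43.9%. Taking 3 months as about 90 days, that is less than one login every 90/30 = 3 days. In the same table the upper quartile of percentage change in intake is +43.5% in that group and +13.1% in the 30–60 login group, so some completers reported drinking more. Under section 6.5 only patients who complete the assessments may be invited to a focus group, so those who dropped out are not heard.

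**5. Time available.**

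- Questions before the block: 5 + 7 + 4 + 5 + 2 = 23. Total: 23 + 4 (block) + 2 (closing) = 29.
- Equal shares of the 90-minute maximum: 90/29 = 3.1 minutes each.
- Start of the block: 23 × 90/29 = 71.4 minutes. Time for the block: 4 × 90/29 = 12.4 minutes. Time for block plus closing: 6 × 90/29 = 18.6 minutes.
- Set-up time is not stated. Assuming 10 to 20 minutes, the block starts at 73.4 to 75.5 minutes and has 11.0 to 9.7 minutes.
- The block is lost entirely only if the first 23 questions average more than 90/23 = 3.9 minutes each, or 75/23 = 3.3 minutes with 15 minutes of set-up.

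**The case against.** The best defence is that the guide as a whole is not one-sided. Question 6 offers helpful or unhelpful, question 9 qualifies benefits, questions 10, 13 and 16 seek negatives, and question 17 allows that the breathalyser did not help. Item 4 of the same block asks about any impact, and the prompt under item 2 asks what other support was used. Participants are told that no answer is wrong. Section 9 also plans correlation and regression of compliance against change in consumption, so the link between app and drinking does not rest on the focus groups alone. All of this stands, and it limits the point to particular items. It does not supply a neutral opening to the block, and a regression cannot give participants' reasons.

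Three stronger readings are tempting, and the documents do not support them.

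- A reader might infer that the whole guide is steered towards benefit. The balanced questions just listed rule that out.
- A reader might infer that all drinking questions come late. The session is planned to begin with experience of alcohol. Questions 2, 4 and 5 cover drinking patterns, motivation for abstinence, steps to stop and triggers for resuming. Only the dedicated questions on the app's effect on behaviour come late. Even their place is uncertain, since the block restarts its numbering at 1 and the closing section resumes at 24.
- A reader might infer that the block is likely to be cut short. The schedule is tight, but the block fits at about 3 minutes per question. Several questions need only a brief answer, and equal shares are a rough model of a group discussion.

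**Conclusion.** The point holds for four items: behaviour-change items 1 and 2 presuppose change, the drinking-habits question is only a conditional prompt, and the question 7 probe covers increased use alone. It is a minor qualitative-methods fault in the measure of one secondary objective. The primary analysis and the numerical results are unaffected.

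The size of any resulting bias cannot be calculated from the documents. The conclusion assumes that moderators keep broadly to the written wording; one who routinely asked the prompt and added neutral follow-ups would remove much of the problem. Moving the block earlier, or trimming questions that the platform log could answer, is a matter of preference and not part of this finding.

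**What to change.** Make four wording changes to the topic guide.

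1. Replace item 1 with a neutral main question, for example: *Did your drinking change at all – up, down or not – while you had the app, and what do you think the reasons were?*
2. Ask item 2 only of participants who report a change.
3. Make the prompt on drinking habits a standard question, worded so that no influence is an acceptable answer.
4. Extend the question 7 probe to using the app more, less, or stopping.

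Keep the probes at questions 17 and 20 on whether features helped. The log can show that a feature was used, but not whether it was useful.

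The cost is a minor amendment to the guide and slightly less time on individual features. Table S5 describes seven people sampled for the qualitative evaluation, so sessions appear to have taken place. For those, report the wording as a limitation and correct the guide before it is used again.

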## **CLOSING**

24. Do you have any final thoughts or comments on how we could improve AlcoChange and the way that it is offered to patients?

25. Any further comments or anything else you would like to add to the discussion?

**Thank you very much for coming**

## Calibration of the AlcoChange breathalyser:

The AlcoChange breathalyser is designed as a battery-less device, which is powered by, and operated through, the smartphone. The attachment to the smartphone is through the 3.5mm connection. Data is securely stored in a cloud platform, and identity of the user is verified through the front smartphone camera before breath alcohol measurements are stored. This feature validates the identity of the individual being tested.

Alcohol content is measured using fuel cell sensors. Calibration is required annually.

Example calibration data is provided below. Six independent alcohol measures were taken in three individuals, at 20 minutes after consumption of 24-32g ethanol. Alcohol was measured by blood content, breath alcohol (BACtrack beathalyser) or AlcoChange breathalyser (Figure S1).

[figure not shown]

**Fig. S1. Calibration of AlcoChange breathalyser against blood alcohol content and BACtrack breathalyser measurement.**  $n=6$  observations, Pearson's correlation performed.
